## Abstract

**Background and Purpose:**

Exercise therapy is a core treatment for knee osteoarthritis (KOA), but the effects of different exercise modalities on endogenous pain modulation remain unclear. This trial will compare a cycling‐based aerobic exercise program with a resistance and neuromuscular exercise program on exercise‐induced hypoalgesia (EIH) in people with KOA and altered baseline EIH.

**Methods:**

This randomized, two‐arm, controlled, single‐blind trial will include 90 participants aged 40–75 years with symptomatic KOA, knee pain intensity of at least 3 points on the Numerical Pain Rating Scale, and altered baseline EIH. Participants will be randomized 1:1 to the Cycling‐Based Aerobic Exercise Group (CAEG) or the Resistance and Neuromuscular Exercise Group (RNEG). Both groups will receive 30 supervised sessions over 10 weeks. The primary treatment effect will be the adjusted mean between‐group difference in within‐session change in pressure pain threshold at the most symptomatic knee, averaged across weeks 1, 4, 7, and 10. Secondary outcomes include EIH at other sites, conditioned pain modulation, pain, self‐efficacy, function, performance, strength, global perceived effect, adherence, and enjoyment.

**Results:**

This trial will evaluate whether the two exercise programs differ in their capacity to elicit EIH in KOA.

**Discussion:**

This trial may clarify whether different exercise modalities produce distinct effects on acute endogenous pain modulation in KOA and may support a more precise exercise prescription for pain management.

**Trial Registration:**

ClinicalTrials.gov, identifier NTC07302204

## Introduction

1

Knee osteoarthritis (KOA) is a prevalent chronic musculoskeletal condition marked by pain, impaired physical function, and reduced quality of life. Osteoarthritis is a heterogeneous, whole‐joint and whole‐person condition influenced by structural, inflammatory, metabolic, biomechanical, and pain‐related mechanisms (Tang et al. 2025; Collins et al. 2026). Therefore, nonsurgical interventions that improve symptoms and support self‐management remain central to rehabilitation (Tang et al. 2025).

Exercise is recommended as a core conservative intervention for KOA, but evidence remains heterogeneous across modalities, doses, progression, follow‐up duration, and outcomes (Gray et al. 2024; Kitagawa et al. 2025; Rausch Osthoff et al. 2026; Schleimer et al. 2026; Viderman et al. 2026). Aerobic, strengthening, neuromotor, mixed, and mind‐body exercises can improve pain, function, gait performance, quality of life, and physical performance (Yan et al. 2025). These findings do not justify prioritizing a single modality for all individuals. Direct comparisons are needed to determine whether relevant exercise programs yield distinct clinical and mechanistic effects.

A comparison of cycling‐based aerobic exercise with resistance and neuromuscular exercise is clinically relevant. Cycling is a low‐impact modality that can be standardized and progressed using perceived exertion, pain, and safety parameters, and may target systemic mechanisms involved in pain modulation (Song et al. 2023; Anderheide et al. 2025). Resistance and neuromuscular exercise are widely used in KOA rehabilitation to improve strength, neuromotor control, function, and movement confidence (Yan et al. 2025). Both approaches may induce exercise‐induced hypoalgesia (EIH), but responses remain variable (Fingleton et al. 2017; Anderheide et al. 2025). It remains unknown whether these programs differ in their capacity to restore EIH in people with KOA who have altered EIH at baseline.

EIH is a short‐term reduction in pain or pain sensitivity following acute exercise and is commonly assessed by pre‐ to post‐exercise changes in pressure pain threshold (PPT) (Wewege and Jones 2021; Song et al. 2023; Toomey et al. 2025). In KOA, responses range from increased PPT to no change or increased pain sensitivity after exercise (Fingleton et al. 2017; Anderheide et al. 2025; Lee et al. 2025; Toomey et al. 2025). This variability is clinically relevant because impaired EIH may influence exercise tolerance, adherence, and clinical response (Song et al. 2023; Lee et al. 2025; Toomey et al. 2025). PPT was selected as the primary mechanistic measure because it quantifies mechanical pain sensitivity and captures the within‐session response used to define EIH. Conditioned pain modulation (CPM) will be assessed as a secondary outcome because it provides complementary information about descending inhibitory function, although CPM and EIH are not interchangeable constructs (Fingleton et al. 2017; Lee et al. 2025).

Clinical and functional secondary outcomes will assess whether mechanistic changes are accompanied by changes in pain, self‐efficacy, knee‐related and patient‐specific function, physical performance, strength, perceived global effect, adherence, and enjoyment. The primary aim was to compare the effects of cycling‐based aerobic exercise and resistance and neuromuscular exercise on knee EIH in individuals with KOA and altered baseline EIH. We hypothesize that the two programs will differ in their capacity to restore knee EIH, as reflected by between‐group differences in within‐session changes in knee PPT over the 10‐week intervention.

## Methods

2

### Study Design and Recruitment

2.1

This randomized, two‐arm, controlled, single‐blind clinical trial will be conducted at the University Clinics of the Nove de Julho University in São Paulo, Brazil. The protocol adheres to the updated CONSORT 2025 and SPIRIT 2025 recommendations and uses the Template for Intervention Description and Replication (TIDieR) checklist to support transparent reporting of the intervention (Hoffmann et al. 2014; Chan et al. 2025; Hopewell et al. 2025) (Supporting Information S1: Table S1).

Recruitment will occur through posters, leaflets, educational talks, and referrals from clinic staff. The target is approximately five eligible participants per month, though this may vary with screening availability and changes in baseline EIH. Screening will include initial contact, informed consent, clinical eligibility assessment, baseline assessment, and randomization only after baseline procedures.

This study was approved by the Research Ethics Committee of Nove de Julho University (No. 93560425.7.0000.5511) and prospectively registered on ClinicalTrials.gov (identifier NTC07302204). Planned recruitment and follow‐up will run from April 2026 to December 2029, aligned with the doctoral timeline and trial logistics. Recruitment may end earlier if the target sample is reached. The same research setting, recruitment sources, and core research team will be maintained throughout the study, whenever possible, to minimize protocol drift and ensure consistency in eligibility assessment, outcome measurement, and intervention delivery.

Recruitment and eligibility assessment will be conducted by two trained physiotherapists using a standardized checklist (Fitzgerald et al. 2015). Before recruitment, the blinded outcome assessor will complete standardized PPT training and a test‐retest reliability assessment in 15 people with KOA. Reliability of the mean of three readings will be estimated using a two‐way mixed‐effects, absolute‐agreement ICC, the standard error of measurement (SEM), and the 95% minimal detectable change (MDC95). An ICC ≥ 0.80 will be required; otherwise, retraining and reassessment will be performed (Stausholm et al. 2023).

Inclusion criteria were men and women aged 40 to 75 years with a prior medical diagnosis of symptomatic KOA, referral for rehabilitation, symptoms for at least 3 months, self‐reported knee pain for more than 3 months, and knee pain intensity of ≥ 3 on the Numerical Pain Rating Scale (NPRS). This age range targets adults commonly affected by symptomatic KOA while minimizing inclusion of younger individuals with secondary knee pain or older individuals with exercise‐limiting comorbidities. KOA will be clinically confirmed using the American College of Rheumatology criteria, defined as knee pain plus at least three of the following: age > 50 years, morning stiffness < 30 minutes, crepitus, bony tenderness, bony enlargement, and absence of palpable warmth (Altman et al. 1986; Zhang et al. 2010).

Participants must also demonstrate altered baseline EIH. After 10 minutes of rest, PPT will be measured using a digital algometer (Force Ten FDX‐25, Wagner Instruments, Greenwich, USA) with a 1 cm^2^ probe, applying pressure at 0.5 kgf/s until the sensation first becomes painful and the participant says “stop” (Rolke et al. 2006; Anderheide et al. 2025).

The PPT will be assessed by the same evaluator at the medial knee compartment of the most symptomatic knee and bilaterally at the upper trapezius. The knee site will be the joint line, 2–3 cm medial to the inferomedial patellar angle, with the participant supine. The remote site will be 10 cm medial to the acromion at C7, with the participant seated. Three measurements will be obtained per site at 30‐second intervals. The mean value will be used, and skin markings will improve reproducibility.

After the baseline PPT assessment, participants will perform an isometric quadriceps contraction of the most symptomatic lower limb in the supine position until voluntary failure or for a maximum of 5 minutes. Total contraction time, knee pain intensity, and perceived exertion will be recorded (Toomey et al. 2025). PPT will be reassessed immediately after exercise at the same marked sites and in the same order.

EIH will be calculated as ΔPPT = post‐exercise PPT minus pre‐exercise PPT, with percentage change also reported (Toomey et al. 2025). Preserved EIH will be defined as ΔPPT > 0 and altered EIH as ΔPPT ≤ 0. Because no validated threshold exists, this is an operational eligibility criterion rather than a diagnostic cutoff. Averaging three readings, standardized sites, skin marking, and the same assessor will reduce measurement error. Baseline ΔPPT will remain continuous in all analyses, and a sensitivity analysis will exclude participants with eligibility ΔPPT values from −MDC95 to 0.

Safety‐related exclusion criteria include cardiovascular or cardiopulmonary contraindications to exercise, deep vein thrombosis or thrombophlebitis, infected wounds or osteomyelitis of the knee, severe osteoporosis or high fracture risk, recent knee trauma, prior arthroplasty of any lower‐limb joint, or neurological disorders that compromise safe exercise participation.

Exclusions include hip symptoms as the primary pain source, fibromyalgia, active inflammatory joint disease, active cancer or cancer‐related pain, clinically significant lower‐limb sensory impairment, cognitive impairment that limits consent or procedure comprehension, use of assistive walking devices, or any other condition deemed to compromise eligibility assessment, intervention safety, adherence, or outcome validity (Fitzgerald et al. 2015).

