### Primary Outcome

2.5

The primary outcome is EIH in the medial knee compartment of the most symptomatic knee, measured as intra‐session change in PPT (ΔPPT) at A1, A4, A7, and A10. The primary estimand is the adjusted mean between‐group difference in ΔPPT averaged across the four sessions. The group‐by‐session interaction and session‐specific differences will be exploratory. PPT will be measured immediately before and after each selected session, and ΔPPT will be the mean post‐exercise value minus the mean pre‐exercise value in kgf/cm^2^. Positive values indicate EIH, zero indicates no EIH, and negative values indicate a hyperalgesic response. If both knees are equally symptomatic, the target knee will be predefined and maintained throughout the trial.

PPT will be measured using a digital algometer (Force Ten FDX‐25, Wagner Instruments, Greenwich, USA) using a 1 cm^2^ probe. Pressure will be applied at 0.5 kgf/s until the sensation first becomes painful and the participant indicates “stop” (Rolke et al. 2006; Anderheide et al. 2025). Three readings will be obtained at the target knee using the same evaluator, in the same order, with 30‐s intervals. The arithmetic mean will be used for analysis, and skin marking will be used to improve site reproducibility.

The knee PPT site will be the medial compartment at the joint line, 2–3 cm medial to the inferomedial angle of the patella, with the participant supine. Intra‐session EIH will be calculated only at A1, A4, A7, and A10. T0 and T1 PPT assessments will characterize baseline and post‐intervention pressure pain sensitivity, not acute EIH.

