### Secondary Outcomes

2.6

Secondary EIH outcomes are intra‐session ΔPPT at the rectus femoris and upper trapezius at A1, A4, A7, and A10. Rectus femoris PPT will be assessed bilaterally with the participant supine, 15 cm proximal to the base of the patella. Upper trapezius PPT will be assessed bilaterally with the participant seated and 10 cm medial to the acromion at the level of C7. For bilateral sites, the right and left values will be averaged for analysis. Chronic adaptation in PPT will be evaluated at T0 and T1 at the knee, rectus femoris, and trapezius.

CPM will be assessed at T0 and T1 using conventional PPT as the test stimulus and ischemic compression as the conditioning stimulus, consistent with CPM testing recommendations (Yarnitsky et al. 2015). Baseline PPT will be measured on the anterior surface of the right forearm, 7.5 cm from the distal wrist crease, using the same algometer and an application rate of 0.5 kgf/s. PPT algometry demonstrates acceptable to excellent reliability in people with KOA (Stausholm et al. 2023). For the conditioning stimulus, an aneroid sphygmomanometer was positioned on the left arm, 3 cm proximal to the cubital fossa, and inflated to 250 mmHg. If pain is < 5 on the NPRS, participants will perform elbow flexion and extension until pain reaches ≥ 5. PPT will then be reassessed on the right forearm while the conditioning stimulus is maintained. After cuff release, PPT will be reassessed at 30 seconds and 5 minutes. CPM will be calculated as the change in PPT during conditioning relative to baseline PPT, with higher values indicating more efficient modulation.

Pain intensity will be assessed at T0 and T1 using the Brazilian Portuguese Numerical Pain Rating Scale (NPRS), ranging from 0 (“no pain”) to 10 (“worst imaginable pain”), for average pain at rest and after movement over the previous 7 days. A 2‐point change will serve as the reference threshold for clinical interpretation (Farrar et al. 2001; Costa et al. 2008).

Pain self‐efficacy will be assessed at T0 and T1 using the Brazilian Portuguese Pain Self‐Efficacy Questionnaire (PSEQ), a 10‐item scale scored from 0 to 60, with higher scores indicating greater self‐efficacy. An 11‐point change will serve as the reference threshold for clinical interpretation (Sardá et al. 2007; Dubé et al. 2021).

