## Statistical Analysis

3

Statistical analyses will follow the intention‐to‐treat principle. The primary outcome will be analyzed using a linear mixed model with fixed effects for group, assessment session (A1, A4, A7, and A10), and group‐by‐session interaction; baseline PPT at the corresponding site will be included as a covariate, with a random intercept for participants.

The primary treatment effect will be the adjusted mean between‐group difference in ΔPPT averaged across the four sessions, estimated using marginal means with 95% confidence intervals and *α* = 0.05. The group‐by‐session interaction and session‐specific contrasts will be exploratory. The covariance structure will be selected using the Akaike Information Criterion from prespecified compound‐symmetry, autoregressive, and unstructured structures.

Continuous secondary outcomes measured at T0 and T1, including KOOS, 30STST, NPRS, CPM, PSEQ, PSFS, and MVIC, will be analyzed using linear mixed models with fixed effects for group, time, and group‐by‐time interaction and a random participant intercept. T1‐only outcomes, including PACES and GPE, will be analyzed using regression models with group as the predictor and an appropriate link function if distributional assumptions are not met.

The primary outcome will be the sole confirmatory outcome because the trial is powered only for it. All secondary outcomes are prespecified but will be interpreted as exploratory and supportive, with emphasis on effect sizes and 95% confidence intervals rather than on confirmatory hypothesis testing.

Clinically important thresholds, when available, will be used only as reference values to support interpretation and not as confirmatory decision rules.

Mixed models will use all available data under the missing‐at‐random assumption. For outcomes not accommodated by mixed models, multiple imputation by chained equations will be used when more than 5% of observations are missing, incorporating group, available baseline and outcome values, adherence, and predictors of missingness. Complete‐case analyses will be sensitivity analyses only. Adherence will be summarized as attendance percentage; a per‐protocol sensitivity analysis will define adequate adherence as ≥ 80%. Protocol deviations, adverse events, and adaptations will be summarized descriptively. Analyses will be conducted in *R*.

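### Small free gain, low severity: adjust the primary model for both pre-randomisation resting PPT readings, and state that T0 is not the eligibility reading

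*Protocol article*

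**What the plan says.** Section 2.1 (Study Design and Recruitment) lists the steps before allocation as "clinical eligibility assessment, baseline assessment, and randomization only after baseline procedures", so eligibility testing and baseline assessment appear as successive steps.

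The eligibility test measures resting PPT at the most symptomatic knee and at both upper trapezius sites, and then: "After the baseline PPT assessment, participants will perform an isometric quadriceps contraction of the most symptomatic lower limb". PPT is repeated after the contraction. The entry rule is: "Preserved EIH will be defined as ΔPPT > 0 and altered EIH as ΔPPT ≤ 0".

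Section 2.5 (Primary Outcome) uses the same word for a different time point: "T0 and T1 PPT assessments will characterize baseline and" post-intervention sensitivity. It adds that these assessments do not measure acute EIH. Section 2.6 (Secondary Outcomes) says: "Chronic adaptation in PPT will be evaluated at T0 and T1 at the knee, rectus femoris, and trapezius". Rectus femoris is in the T0 set but not in the eligibility test.

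Section 3 (Statistical Analysis) says of the primary model that "baseline PPT at the corresponding site will be included as a covariate". It does not say which resting reading is meant.

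**The concern.** One word, *baseline*, covers two resting readings at the knee and trapezius, and two questions follow.

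1. **Precision.** If T0 is a fresh measurement, two pre-randomisation readings of the same quantity exist. Each carries measurement error, and adjusting for only one leaves information unused. This matters a little here because the sample size leans on the baseline covariate. Section 2.2 gives 39 per group at a correlation of 0.60, against 55 at 0.30 and 60 at 0, and describes the resulting power as only close to 80%.

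2. **The starting value for chronic change.** The two readings are not equivalent. A candidate enters only if the post-exercise PPT does not exceed the pre-exercise PPT, which favours pre-exercise readings that are too high by chance. If that reading were ever used as T0, resting PPT would appear to fall by T1 without any real change.

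**Working it through.** **Inputs from the protocol (sections 2.1, 2.2 and 3).** ΔPPT SD 0.70 and target difference 0.30 kgf/cm²; four sessions with within-participant correlation 0.60; correlation of baseline PPT with the four-session mean 0.60; α = 0.05 as in section 3; 80% power; 38 evaluable per group after attrition; ICC of at least 0.80 required of the PPT mean of three.

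**Assumed, because the protocol gives no figure.** Reliability R of one resting reading: 0.80 to 0.90. Error SD of one resting reading: 0.20 to 0.40 kgf/cm². Mean ΔPPT among candidates screened: 0 to 0.30 kgf/cm². Pre- and post-exercise errors independent.

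**Step 1: the plan's own figure.**
- Variance of the participant mean: 0.70² × (1 + 3 × 0.60)/4 = 0.343, SD 0.586.
- Residual SD: 0.586 × √(1 − 0.60²) = 0.469.
- n = 2 × 7.849 × 0.343 × 0.64/0.09 = 38.3, so 39 per group. This reproduces section 2.2.
- Power at 38 per group: Φ(0.30/(0.4685 × √(2/38)) − 1.96) = Φ(0.831) = 79.7%.

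**Step 2: both readings in the covariate.** For the mean of two readings with equal error, r² becomes 0.36 × 2/(1 + R).

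| R | r | Residual SD | n per group | Power at 38 per group |
|---|---|---|---|---|
| one reading | 0.600 | 0.469 | 38.3 | 79.7% |
| 0.80 | 0.632 | √(0.343 × 0.600) = 0.454 | 35.9 | 82.2% |
| 0.90 | 0.616 | √(0.343 × 0.621) = 0.462 | 37.2 | 80.9% |

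The residual variance falls by 1 − 0.600/0.64 = 6.3% (R = 0.80) or 1 − 0.621/0.64 = 3.0% (R = 0.90).

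**Step 3: does the entry rule spoil this?** The formula treats the two readings as exchangeable, although one of them has been selected. Simulation with selection on ΔPPT ≤ 0 built in gives a residual SD of about 0.453 to 0.462 and power of about 81 to 82%. The gain survives.

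**Step 4: a weaker correlation.** At 0.30, r² becomes 0.09 × 2/1.8 = 0.100 or 0.09 × 2/1.9 = 0.095. The residual variance falls by 1 − 0.900/0.91 = 1.1% or 1 − 0.905/0.91 = 0.5%.

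**Step 5: upward selection of the eligibility reading.** Mean error given entry = (error SD)²/0.70 × φ(a)/Φ(a), with a = −(mean ΔPPT)/0.70.
- Mean 0, error SD 0.20: 0.04/0.70 × 0.798 = 0.046.
- Mean 0.15, error SD 0.30: 0.09/0.70 × 0.939 = 0.121.
- Mean 0.30, error SD 0.40: 0.16/0.70 × 1.089 = 0.249.

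The range is about 0.05 to 0.25 kgf/cm². In simulations with no true change, using this reading as T0 gives the same spurious fall in both arms (for example −0.14 in each at error SD 0.35 and mean 0). A separate T0 reading gives a change of 0.00. The between-arm difference is about 0 in both cases.

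**The case against.** The strongest reply is that nothing here is an error. The successive steps in section 2.1, the separation of T0 from acute EIH in section 2.5 and the presence of rectus femoris only at T0 all point to a separate T0 reading. With a separate T0, the T0–T1 change has no selection artefact. Adjusting for one baseline value is standard practice, and either reading is a valid covariate. All of this stands.

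A reader might infer that the protocol starts its chronic-change comparison from an inflated value. The text does not support that: it nowhere says that the eligibility reading serves as T0, and it leans the other way. A reader might also infer that the primary contrast is biased. It is not, because the entry rule acts before randomisation and equally on both arms.

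The two issues are also alternatives. If T0 is separate, there is a second reading to use and no artefact. If T0 were the eligibility reading, there would be an artefact and no second reading.

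The sizes rest on assumptions. The SD of 0.70 comes from within-session change in a feasibility trial, not from this isometric screening test. Error shared by pre- and post-exercise readings in one visit cancels in ΔPPT and is not selected, so an error SD that includes it would overstate the inflation. Nor is the target of 0.30 a yardstick for the inflation: it is a between-group difference in ΔPPT, not a within-arm change in resting PPT.

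What remains is that the argument for a separate T0 is also the argument that two readings exist, and the model names only one, without saying which.

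**Conclusion.** This is an optional, low-severity improvement and does not show that the plan is wrong. If T0 is a separate reading, as the text implies, entering both resting knee readings lowers the residual SD from 0.469 to about 0.453–0.462 and raises power at 38 per group from 79.7% to about 81–82%, worth roughly one to two and a half participants per group (38.3 to 35.9–37.2). That depends on the plan's correlation of 0.60 and on an assumed reliability of 0.80 to 0.90. If the correlation is nearer 0.30, the gain is about 1% of variance or less.

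The T0 point is a safeguard against a conditional risk. It would affect only the within-arm change in one exploratory outcome, by about 0.05 to 0.25 kgf/cm² under the stated assumptions, and never the comparison between arms.

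**What to change.** 1. In section 3, replace the unspecified covariate with both pre-randomisation resting knee readings (eligibility pre-exercise and T0), entered as their mean or as two covariates. Do the same for the trapezius EIH model. Rectus femoris has only the T0 reading and needs no change.
2. In section 2.6, state that the starting value for chronic PPT change is the separate T0 reading and not the eligibility pre-exercise reading. In section 2.1, give the latter a name other than *baseline*.

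The cost is two or three sentences and at most one model degree of freedom. If T0 is already taken separately, no new measurement is needed. This should be confirmed before enrolment, because a separate pre-treatment reading cannot be obtained afterwards.

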### Sample Size

2.2

The sample size was calculated for the prespecified primary estimand, the adjusted mean between‐group difference in knee ΔPPT averaged across A1, A4, A7, and A10. The target difference of 0.30 kgf/cm^2^ and the standard deviation of 0.70 kgf/cm^2^ were taken from the within‐session knee PPT change in the feasibility trial of Anderheide et al. (2025). Under compound symmetry with four measurements and a within‐participant correlation of 0.60, the standard deviation of the participant‐level mean is 0.586 kgf/cm^2^ [0.70 × √((1 + 3 × 0.60)/4)]. Assuming a correlation of 0.60 between baseline PPT and that mean, covariate adjustment gives a residual standard deviation of 0.469 kgf/cm^2^ [0.586 × √(1 − 0.60^2^)].

With a two‐sided *α* of 0.05% and 80% power, *n* = 2(z_1_−α/_2_ + z_1_−β)^2^σ^2^/δ^2^ gives 38.3, that is 39 evaluable participants per group (R 4.4.1). Allowing for approximately 15% attrition, 45 participants per group will be recruited, a total of 90, retaining at least 38 evaluable participants per group and power close to 80%. The estimate depends on the assumed baseline correlation: 55 and 60 participants per group would be needed for correlations of 0.30 and 0.

Compound symmetry is a planning assumption, since the analysis will select the covariance structure empirically. Because no established minimal clinically important difference exists for EIH assessed by PPT in KOA, 0.30 kgf/cm^2^ is an a priori planning target rather than a clinical threshold.

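### Baseline ΔPPT is said to stay continuous in all analyses, yet no model includes it; adding it to the primary model may gain precision at the cost of one degree of freedom

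*Protocol article*

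**What the plan says.** Section 2.1 (Study Design and Recruitment) makes a baseline EIH test a condition of entry: "Participants must also demonstrate altered baseline EIH". PPT is measured, "participants will perform an isometric quadriceps contraction of the most symptomatic lower limb", and PPT is measured again. The section defines "altered EIH as ΔPPT ≤ 0", calls this an operational eligibility rule, and then states "Baseline ΔPPT will remain continuous in all analyses". It also plans a sensitivity analysis that drops participants whose eligibility value lies between −MDC95 and 0. The Discussion again names continuous analyses among the ways to deal with the uncertainty of the cutoff.

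Section 3 (Statistical Analysis) gives the primary model: group, session, group-by-session interaction and a random participant intercept, and "baseline PPT at the corresponding site will be included as a covariate". The models for outcomes measured at T0 and T1, and those for T1-only outcomes, do not name baseline ΔPPT either.

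Section 2.2 (Sample Size) takes its variance reduction from the PPT level: "Assuming a correlation of 0.60 between baseline PPT and that mean". Section 2.5 (Primary Outcome) says that "T0 and T1 PPT assessments will characterize baseline and post"-intervention pressure pain sensitivity, and that they do not measure acute EIH.

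**The concern.** Section 2.1 makes a positive statement about every analysis, and Section 3 contains no analysis to which it applies. The two stated uses of baseline ΔPPT, the entry cutoff and the MDC95 exclusion, are both categorical. A reader cannot tell whether the value was meant to be in the primary model.

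Two things are at stake. The first is precision. The outcome is a post-minus-pre change, and the only adjustment is for a level. A measured pre-randomization change of the same kind goes unused, and chance imbalance in it is not adjusted for. The second is prespecification. This is the only confirmatory analysis, and if the two sections are reconciled only after the data are seen, the covariate set becomes a post hoc choice.

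**Working it through.** **Inputs from Section 2.2.** "The target difference of 0.30 kgf/cm^2^ and the standard deviation of 0.70 kgf/cm^2"; within-participant correlation 0.60 over four sessions; correlation 0.60 between baseline PPT and the four-session mean; 80% power; at least 38 evaluable per group. Two-sided alpha is taken as 0.05, as in Section 3. Section 2.2 prints it with a percent sign, but its sample size is reproduced only with 0.05.

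**Step 1: reproduce the plan.**
- SD of the four-session mean = 0.70 × √((1 + 3 × 0.60)/4) = 0.586.
- Residual SD = 0.586 × √(1 − 0.60²) = 0.469.
- n = 2 × (1.960 + 0.842)² × 0.469²/0.30² = 38.3 with unrounded values, so 39 per group. This matches.
- Correlations of 0.30 and 0 give 54.4 and 59.8, so 55 and 60. These match too.
- Power at 38 per group = Φ(0.30/(0.469 × √(2/38)) − 1.960) = 0.797, in line with the article's description of power close to 80%. At a correlation of 0 it is 0.608. The t-based values are 0.787 and 0.596.

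**Step 2: baseline PPT performs as planned (correlation 0.60) and ΔPPT is added.** The article gives no correlation for eligibility ΔPPT, so its partial correlation r_p with the outcome mean, given baseline PPT, is an assumption. Residual SD = 0.469 × √(1 − r_p²).

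| r_p (assumed) | Residual SD | Power at 38 per group, normal | Power, t-based |
|---|---|---|---|
| 0 | 0.469 | 0.797 | 0.787 |
| 0.2 | 0.459 | 0.813 | 0.803 |
| 0.3 | 0.447 | 0.833 | 0.823 |
| 0.4 | 0.429 | 0.861 | 0.852 |
| 0.5 | 0.406 | 0.897 | 0.889 |

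**Step 3: baseline PPT explains nothing and ΔPPT is added.** Assume a single-session correlation r_s between eligibility ΔPPT and each session's ΔPPT. Before selection, its correlation with the four-session mean is r = r_s/√((1 + 3 × 0.60)/4). For r_s = 0.60 this is 0.60/0.837 = 0.717. For r_s = 0.30 it is 0.359.

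Selecting ΔPPT ≤ 0 narrows the covariate's range. Assume a normal ΔPPT with SD 0.70 and mean μ before selection. With b = −μ/0.70 and λ = φ(b)/Φ(b), the SD shrinks by u = √(1 − bλ − λ²). For μ = 0, u = 0.603; for μ = 0.30, u = 0.529. The restricted correlation is ru/√(1 − r² + r²u²). The outcome SD is held at the plan's 0.586.

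| r_s (assumed) | μ | Restricted r | Variance removed | Power at 38 per group, normal | Power, t-based |
|---|---|---|---|---|---|
| none | – | 0 | 0% | 0.608 | 0.596 |
| 0.30 | 0.30 | 0.199 | 4% | 0.625 | 0.614 |
| 0.30 | 0 | 0.226 | 5% | 0.630 | 0.619 |
| 0.60 | 0.30 | 0.478 | 23% | 0.720 | 0.709 |
| 0.60 | 0 | 0.527 | 28% | 0.748 | 0.737 |

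The two power methods differ by about 0.01 throughout. The ranges cited elsewhere in this point use the normal approximation for Step 2, which is the plan's own method, and the t-based values for Step 3.

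**The case against.** The strongest reply is that the sentence in Section 2.1 follows directly on the cutoff and may mean only that ΔPPT will not be dichotomized wherever it is used. On that reading it promises no covariate, and one edited sentence would settle the matter. The reading is fair. It does not remove the problem, because the article names no continuous use anywhere, and the Discussion relies on such analyses.

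A reader might draw four stronger conclusions, and the article supports none of them.

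- *The plan omits the baseline value of the outcome itself.* Site, device and formula match, but the stimulus is one isometric contraction and not a cycling or resistance session. Eligibility ΔPPT is a close analogue, and how well it predicts the outcome is not known from the article.
- *The sections conflict on what baseline means in the primary model.* They do not. Sections 2.2 and 3 both use baseline PPT, and Section 2.1 does not describe the primary model.
- *The omission biases the result.* Allocation is randomized and concealed, so leaving out a prognostic covariate biases neither the group contrast nor its type I error. Chance imbalance is already reflected in the confidence interval.
- *A large gain is being lost.* The upper figures in Step 3 borrow the between-session 0.60 for a different stimulus and set the contribution of baseline PPT to zero. Eligibility ΔPPT also contains a pre-exercise knee PPT, so it may overlap with the covariate already in the model. With a single-session correlation of 0.30, the gain is about two points of power.

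**Conclusion.** The point holds as a mismatch between Sections 2.1 and 3 and as a likely missed improvement. The plan's sample size is correct on its own inputs, and the planned analysis is valid without the extra covariate.

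The possible gain is in precision only, and its size is uncertain. With baseline PPT at the planned 0.60, power at 38 per group moves from about 0.80 to 0.81–0.90 for an assumed partial correlation of 0.2–0.5. If baseline PPT explains nothing, it moves from about 0.60 to 0.61–0.62 or to 0.71–0.74, for assumed single-session correlations of 0.30 and 0.60 after range restriction. The second case deserves attention because the article cites no source for the 0.60 between a PPT level and a PPT change, and itself shows that the required sample grows to 60 per group without it. The absence from the models is certain; the benefit rests on assumed correlations.

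**What to change.** In Section 3, add eligibility knee ΔPPT, continuous and linear, as a prespecified fixed covariate beside baseline knee PPT in the primary model, so that the model agrees with Section 2.1. Eligibility trapezius ΔPPT may be used in the same way for the exploratory trapezius outcome. The rectus femoris is not tested at eligibility, so it has no value of its own and no change is proposed there.

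The cost is one degree of freedom. The value is already collected from every participant before randomization, and the sample size need not change. If the sponsor prefers the present model, Section 2.1 and the matching remark in the Discussion should say where continuous ΔPPT is used, or drop the statement; that gives up the possible precision. Either way, the choice should be fixed before unblinding.
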